### Randomization and blinding

A blocked randomization method stratified by NICU will be used to assign infants to either the control or fresh milk groups. Infants from multiple-birth pregnancies will be randomized to the same group. We will use an online software application (https://www.graphpad.com/quickcalcs/randomize1.cfm) to generate the allocation scheme and randomize patients electronically. If the parents wish to withdraw consent at any time, all study procedures will cease, and the infant will be fed following the current standard procedures for human milk handling and feeding as directed by the clinical team.

The study will be double blinded; thus, the medical and nursing teams caring for the infants will be unaware of the type of human milk used for feeding. A research nurse will label the milk with only the study site and infant number and deliver the milk to the nurse caring for the baby, who will be blinded to whether the baby is receiving fresh or frozen human milk. The outcomes of the infants will be collected by an investigator blinded to the group allocation. Data analysis will be performed using a binary treatment code to maintain group allocation of blinding until the results are finalized. No unblinding will occur in this study.

### Timeline

#### Preparation (July 1, 2018, to December 31, 2018)

During the preparation phase, we will develop and implement an education program for staff [19] regarding the study protocol, which will include in-service sessions held before the study period begins. Furthermore, we will obtain approval from the research ethics boards as required for the study protocol, and then we will implement the required changes to unit feeding policies (Fig. 1, Additional file 3).

#### Enrollment (January 1, 2019, to December 31, 2020)

The enrollment phase of the study will continue until 1549 infants and their mothers have completed the fresh milk protocol and 1549 infants and their mothers have completed the control protocol. Data collection will begin when the first infant is enrolled and will be completed when the last infant has reached 32 weeks’ corrected age.

#### Project completion (January 2, 2021, to June 30, 2021)

During the project completion phase, any outstanding data will be collected and entered, data will be cleaned up and analyzed, and the study results will be reported.

### Data collection

We will collect data from January 1, 2019, to December 31, 2020, on maternal and infant characteristics including demographics, risk factors, delivery complications, illness severity scores, infant complications, weight, growth, and daily feeding practices, including probiotics. All information will be collected on data forms, with data being entered into an encrypted excel file database for subsequent analysis. Study-specific variables will include compliance with the fresh milk protocol, the number and volume of fresh milk feeds provided to study infants on each day, and the response of the infant following the feed (Additional file 4). Outcomes will be assessed at 32 weeks’ corrected age. For completion and to allow collection of outcomes that can only be assessed beyond 32 weeks (e.g., BPD), outcomes will also be collected at discharge. For infants discharged before 32 weeks’ corrected age, we will follow up until they reach 32 weeks’ corrected age and record data on the primary and secondary outcomes. All data will be de-identified, and we will use patient numbers instead of names when summarizing data. Data access will comply with privacy regulations, and all data will be kept by a specialist to protect the patients’ privacy.

The Research Institute of Children’s Hospital of Fudan University in Shanghai, China, will host the coordinating center for the Fresh Milk study. The coordinating center will store all the study data and complete data analysis. [name] from the Children’s Hospital affiliated to Zhengzhou University will be the Principal Investigator of the study and will be responsible for registering, receiving ethical approval, and notifying and receiving approval for changes to the study from the regulatory bodies. Central ethical approval was confirmed from the ethics committee of the Children’s Hospital affiliated to Zhengzhou University for Clinical Research (REB #2018042701, Additional file 3), and we will not begin recruiting at other centers in the trial until local ethical approval has been obtained. The study is registered in the Chinese Clinical Trial Registry (www.chictr.org.cn) #ChiCTR1900020577. To ensure ethical standards are met, we will obtain informed consent from each participating parent before enrollment and will respect the parents’ decision to join or leave the study at any time. Furthermore, we will use an incident reporting system that will be completed within 24 h of an incident and will include a formal written report to protect the patients’ safety. Finally, we will obtain the parents’ written approval for publishing their names or pictures on the research update in addition to following the data privacy procedures described above.

### Sample size

The sample size justification was based on the primary outcome and the hypothesis. A recent quality improvement study found that the incidence of the composite outcome mortality or NEC ≥ stage 2 was 29% in 25 Chinese NICUs [[name], written communication, October 2018]. Assuming a primary outcome rate of 29% for the control group, we estimated that a sample size of 3098 (1549 patients per arm) will achieve an 80% power to detect at least a 16% relative reduction in the incidence of the primary outcome in the fresh milk group when compared to the control group. With an average of 2397 eligible infants admitted to participating hospitals each year and an estimated enrollment rate of 60%, we expect to recruit 1438 infants per year and the study to take 2 years. We used the chi-square test for the power analysis, assuming a significant level of 0.05. Therefore, the proposed enrollment of 3098 patients will have sufficient power to test our hypothesis taking into account a possible 5% data loss to follow-up.

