*Cytomegalic virus* infection acquired from fresh human milk has been discussed as a potential safety concern in preterm infants [48]. However, the issue is controversial, and guidelines vary [49]. Some guidelines recommend that preterm infants are fed pasteurized mother’s own milk because of the potential risk of contamination by CMV. However, this may be unnecessary considering that if a mother is CMV positive, the infant already will have been exposed to CMV *in utero*. We will address this concern in our study by requiring every neonate admitted to the NICU to be tested for CMV and pasteurizing infected milk before use.

Oxidative stress is a major problem for ill infants and for preterm infants in particular; therefore, energy intake and antioxidant defense are crucial for preterm infants’ wellbeing [﻿45﻿]. Very preterm infants have diminished antioxidant capacity and are frequently exposed to oxidative stress from multiple sources such as infection, oxygen therapy, and mechanical ventilation. Furthermore, excess oxygen can secondarily lead to retinopathy of prematurity or chronic lung disease in preterm infants [﻿45﻿]. NEC, intraventricular/periventricular hemorrhage, and retinopathy of prematurity are all thought to be consequences of the imbalance between antioxidant capacity and oxidative stress [50]. Previous studies reported that human milk has important and essential antioxidant components, which may prevent and protect against diseases in infancy [45]. Human milk feeding remains an essential tool to help in the protection against free radicals, oxygen reactive species and oxidative stress, with fresh human milk having been reported to have the highest antioxidant activity [﻿45].

Our study will have some limitations. One limitation is a potential drop-out rate of 10% of enrolled families (based on our pilot study data) [﻿19﻿] due to factors such as time constraints. To minimize the potential bias from families leaving the study, we will use intention-to-treat analysis. If applicable, we will also conduct regression adjusted for propensity score estimated based on the infant and NICU characteristics available. Last, in China, approximately 17% of infants born preterm per year are discharged against medical advice and die at home. These infants will be included in our intention-to-treat analysis. To address this concern, we will perform a subgroup analysis of the primary outcome that only includes infants who were actively treated.

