## Trial status

The current protocol version is 4 on October 2, 2018. Patient recruitment began January 1, 2019, and should be completed by December 31, 2020.

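### The recruitment forecast, enrollment dates, rule for ending enrollment and loss rates do not fit together: two years at the forecast rate gives 2876 infants, not 3098

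*Protocol article*

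**What the plan says.** **Size and power (Protocol article, Sample size).** The inputs are "Assuming a primary outcome rate of 29% for the control group" and the aim to "detect at least a 16% relative reduction in the incidence of the primary outcome in the fresh milk group". On these, "a sample size of 3098 (1549 patients per arm) will achieve an 80% power". The method is given as "We used the chi-square test for the power analysis, assuming a significant level of 0.05", and the proposed enrollment of 3098 is described as "taking into account a possible 5% data loss to follow-up".

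**Recruitment (same section).** From 2397 eligible infants a year and 60% enrollment, "we expect to recruit 1438 infants per year and the study to take 2 years".

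**Dates and rule for ending enrollment.** The Enrollment part of the Timeline section runs from 1 January 2019 to 31 December 2020. Its text continues enrollment until 1549 infants in each arm have completed their protocol. Trial status repeats the dates: "Patient recruitment began January 1, 2019, and should be completed by December 31, 2020".

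**Drop-out (Discussion, limitations).** Citing the pilot study, the authors name a "potential drop-out rate of 10% of enrolled families", to be handled by intention-to-treat analysis and, if applicable, a propensity-score adjustment.

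**The concern.** The forecast rate multiplied by the stated duration should give the stated sample, and it does not. The dates leave no slack: the window is exactly the two years of the forecast. The Data collection section also bars recruitment at the other centers until local ethical approval is in place, so a full 1438 in the first year is already a favourable assumption.

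Two further statements make it unclear what happens when the shortfall appears. The Timeline section gives both a date and a completion count for the end of enrollment. The count is of completers, whereas the Sample size section treats the same 3098 as enrolled infants. In addition, the loss allowance is half the drop-out rate that the authors take from their pilot, and no reason is given.

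If the count governs, the trial runs past its stated end date. If the date governs, it closes with fewer infants than the power statement assumes. The article does not say which applies.

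**Working it through.** **Inputs.** From Sample size: control rate p1 = 0.29; 16% relative reduction, so p2 = 0.29 × 0.84 = 0.2436 and d = 0.0464; power 80%; chi-square test at 0.05; 5% loss; 2397 eligible per year at 60%. From Statistical analysis: two-sided testing. From Background: 1:1 allocation. From Discussion: 10% drop-out.

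**Step 1: reproduce the stated sample size.** With p̄ = 0.2668,

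n = [1.960·√(2p̄(1−p̄)) + 0.842·√(p1(1−p1) + p2(1−p2))]² / d² = 1426 per arm.

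With the continuity correction, n' = (n/4)·[1 + √(1 + 4/(n·d))]² = 1468 per arm. Allowing for 5% loss, 1468/0.95 = 1546 per arm, or 3092 in total, against the stated 1549 and 3098. The target reproduces. Without the correction, 1426/0.95 = 1502. The corrected formula also returns exactly the 1146 per arm given for the actively treated subgroup (17%, 25% relative reduction), so it is probably the one used.

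**Step 2: recruitment.**
- 2397 × 0.60 = 1438 per year; × 2 = 2876.
- 3098 − 2876 = 222, and 222/3098 = 7.2%.
- 3098/1438 × 12 = 25.9 months.
- Enrollment rate needed to reach 3098 in 24 months: 3098/(2 × 2397) = 64.6%.

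**Step 3: if 3098 must complete.** Loss then has to be added on top.
- 5% loss: 3098/0.95 ≈ 3262 enrolled; 3262/1438 × 12 = 27.2 months.
- 10% loss: 3098/0.90 ≈ 3443 enrolled; 3443/1438 × 12 = 28.7 months.

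**Step 4: power.** With n infants per arm contributing an outcome,

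power = Φ{[d − c − 1.960·√(2p̄(1−p̄)/n)] / √([p1(1−p1) + p2(1−p2)]/n)},

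where c = 0 for the plain test and c = 1/n with continuity correction.

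| Enrolled | Outcomes lost | n per arm | Power, plain | Power, corrected |
|---|---|---|---|---|
| 3098 | 5% | 1471 | 81.2% | 80.1% |
| 3098 | 10% | 1394 | 79.1% | 77.9% |
| 2876 | none | 1438 | 80.4% | 79.2% |
| 2876 | 5% | 1366 | 78.3% | 77.0% |
| 2876 | 10% | 1294 | 76.1% | 74.7% |

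On the plain formula, 2876 enrolled with 10% loss has 80% power for a relative reduction of 16.8%, about 17%.

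**The case against.** A reader might infer from the shortfall that the stated 80% power is not met. The documents do not support that, for three reasons.

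1. The power statement is made for 3098 infants with 5% loss, and on those terms it is correct (80–81%).
2. The Timeline section continues enrollment until a count is reached, and Trial status says only that recruitment should be finished by the end of 2020. If the count governs, slow accrual costs time and not power.
3. The 5% is loss of outcome data, whereas the 10% is families leaving for reasons such as time constraints. Under intention-to-treat these can differ. The Human milk collection section keeps mothers who give too few fresh feeds, and the Data collection section follows infants discharged early to 32 weeks. The two figures are therefore not a plain contradiction.

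It can also be said that 2397 is an average, 60% is an estimate, and two years for 2.15 is loose rounding.

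Most of this stands, and it limits the point to consistency. It does not remove the point. The completion rule sits under a dated heading that ends enrollment on 31 December 2020, and it conflicts with a sample size that already includes loss. On the two loss rates, the Randomization and blinding section stops all study procedures on withdrawal and does not say whether outcomes are still collected. The Statistical analysis section treats drop-out and missing data together. How far the 10% becomes lost outcomes is therefore unknown.

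**Conclusion.** The point holds as an inconsistency among the forecast, the dates, the rule for ending enrollment and the loss rates. On the plan's own figures, 24 months yields 2876 infants, 222 (7.2%) short, and 3098 takes about 26 months.

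The effect on power is conditional and modest. Against an 80% target:
- 78–79% if 3098 are enrolled and the full 10% lose their outcome;
- 77–78% if enrollment closes at 2876 with 5% of outcomes lost;
- 75–76% if it closes at 2876 with 10% lost.

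These figures assume the stated 29% rate, the 16% relative reduction, independent infants, and recruitment at exactly 1438 per year from the first day. The 10% cases further assume that every family that drops out takes its infant's outcome with it, which the article neither states nor excludes. The conclusion that the sample size is too small for its own assumptions is not supported.

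**What to change.** 1. State whether enrollment ends by count or by date, and whether 3098 means infants enrolled or infants completed. Use the same meaning in Sample size, Timeline and Trial status.
2. Use one outcome-loss figure throughout, or state that outcomes are still collected after families drop out, which would justify 5% beside a 10% drop-out.
3. Restate the figure that follows:
   - **By count:** a duration of about 26 months for 3098 enrolled, or about 27 to 29 months if 3098 must complete. If 10% of outcomes are lost from 3098 enrolled, give power as 78–79%. Extending to 26 months does not by itself restore 80% at that loss: on the continuity-corrected formula this needs 1468/0.90 = 1632 per arm (3264 in total, about 27 months).
   - **By date:** expected enrollment of 2876, with power of about 77–78% at 5% loss, or 75–76% at 10% loss (80% power for about a 17% relative reduction).

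The cost is a change of text, plus either a slightly less favourable stated power or a longer stated timeline. No analysis method changes.

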### Statistical analysis

Data from the study will be analyzed on an intention-to-treat basis. Patient characteristics at baseline will be summarized within each of the groups using the descriptive statistical methods suggested by the CONSORT statement for randomized clinical trials. To examine the difference in the rate of the primary outcome between the control and fresh human milk groups, we will use the chi-square test. We will compare the secondary outcomes of the control and fresh milk groups using the chi-square test or Fisher exact test, as appropriate, for categorical variables and the Student T test or Wilcoxon Rank Sum test, as appropriate, for continuous variables.

As secondary analyses, we will also, if applicable, determine whether a variation exists in the treatment effect across the centers/NICUs by presenting the effects by individual centers/NICUs graphically. If variation is observed, we will further compare the binary outcomes using the Cochran-Mantel-Haenszel test to account for the effect of center, as well as conducting fixed-effect logistic regression (for binary outcomes) or linear regression (for continuous outcomes) without including treatment-center interaction term. The fixed-effect model including treatment-center interaction term will be further applied to examine the heterogeneity of the effect across centers when the variation in the center-effect is identified. If variation exist in the center-effect but no heterogeneity of the effect is observed, a marginal logistic or linear regression model with generalized estimating equations (GEE) approach will be applied to estimate the main treatment effect to account for the center effect. If the heterogeneity of the effect is observed, subgroup analysis stratified by the homogeneous centers using marginal models with GEE approach will be applied if applicable.

To examine whether a variation exists in the treatment effect across gestational age group (i.e., GA < 28 vs GA: 28–30), birth weight group (i.e., BW < 1000 g vs BW: 1000-1500 g) or upon receipt of probiotics, fixed-effect logistic or linear models will be used that include GA (or BW or probiotic) group and the interaction between treatment and GA group (or BW or probiotic), if applicable.

In China, approximately 17% of infants born preterm die at home following discharge against medical advice [[name], written communication, October 2018]. Since we are using intention-to-treat analysis in our study, these infants will be included in our analysis. However, we will perform a subgroup analysis that only includes infants who were actively treated, which includes 1991 infants per year on average [[name], written communication, October 2018]. The primary outcome rate is 17%, on average, for infants who are actively treated; therefore, we estimate that a total sample size of 2292 infants (1146 per arm) will achieve an 80% power to detect at least a 25% relative reduction in the incidence of the primary outcome in the fresh milk group when compared to the control group.

We will also apply linear or nonlinear mixed-effect models for the longitudinal secondary outcomes (weight or change in weight z-score over time) to compare the rate of the change in the outcomes between the two groups, adjusted for the infant- and NICU- level characteristics if applicable. For secondary outcomes, no adjustment for multiple comparisons will be conducted.

For the primary outcome, to minimize possible bias due to drop out or missing data, we will also, if applicable, conduct logistic regression adjusted for propensity score estimated based on the infant and NICU characteristics available. A two-sided *p* value of < 0.05 will be used to determine the statistically significant difference.

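### The primary comparison is an unadjusted chi-square test, although gestational age and birth weight are fixed at birth; a pre-specified adjusted analysis would add about 2 to 10 points of power, depending on an assumed prognostic strength

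*Protocol article*

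**What the plan says.** The Statistical analysis section of the protocol article fixes the primary test: "To examine the difference in the rate of the primary outcome between the control and fresh human milk groups, we will use the chi-square test". The Sample size section uses the same test: "We used the chi-square test for the power analysis, assuming a significant level of 0.05". Significance is judged two-sided: "A two-sided *p* value of < 0.05 will be used to determine the statistically significant difference".

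Infant-level prognostic data appear in three other places:

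- Data collection lists "maternal and infant characteristics including demographics, risk factors, delivery complications, illness severity scores" among the items recorded, and goes on to items such as growth and daily feeding. It does not say when illness severity is scored.
- The subgroup paragraph of Statistical analysis says "fixed-effect logistic or linear models will be used that include GA (or BW or probiotic) group and the interaction between treatment and GA group". Gestational age and birth weight are each cut into two groups there, and serve to test interaction.
- Later in the same section, to limit bias from drop-out or missing data on the primary outcome, the investigators will, if applicable, "conduct logistic regression adjusted for propensity score estimated based on the infant and NICU characteristics available".

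Statistical analysis also plans centre-adjusted analyses of the treatment effect (Cochran-Mantel-Haenszel, fixed-effect logistic regression, GEE). These are secondary and depend on whether variation between centres is seen.

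**The concern.** Infants at every gestation below 30 weeks are eligible, so some of the variation in death or NEC should follow from how immature and small each infant is at birth. The chi-square test leaves that variation in the error term. Randomisation is stratified by NICU only, so chance differences between arms in gestational age or birth weight also stay in the estimate as random error.

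Both covariates are available. Eligibility rests on gestational age, and the standard feeding schedule depends on birth weight. A pre-specified adjusted analysis would use them to sharpen the primary comparison without enrolling anyone else. At stake is precision on the trial's main question, in a design whose stated power is only 80%.

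**Working it through.** **Inputs.** From Sample size: control rate 29%, 16% relative reduction, 1549 per arm, 5% loss to follow-up. From Statistical analysis: two-sided 0.05. Assumed, because the documents give no figure: R², the share of outcome variance explained by baseline covariates.

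**Step 1: reproduce the plan's figure.**
- Fresh-milk rate: 0.29 × 0.84 = 0.2436. Difference d = 0.0464. Mean rate p̄ = 0.2668.
- Sum of variances: v = 0.29 × 0.71 + 0.2436 × 0.7564 = 0.2059 + 0.1843 = 0.3902.
- Without continuity correction: n = [1.96 √(2p̄(1−p̄)) + 0.842 √v]² / d² = 1426 per arm.
- With continuity correction: (n/4)[1 + √(1 + 4/(nd))]² = 1468 per arm.
- Allowing for 5% loss: 1468 / 0.95 = 1546, against 1549 stated. The figure reproduces to within 0.2%.
- Evaluable after 5% loss: 1549 × 0.95 = 1471.55, taken as 1472 per arm. Chi-square power there is 80.1% with continuity correction and about 81.2% without.

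So the planned test reaches the planned power.

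**Step 2: effect of adjustment.** With covariates explaining a share R² of the outcome variance,

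Power = Φ( d / √(v(1 − R²)/n) − 1.96 ), n = 1472.

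For R² = 0 the standard error is √(0.3902/1472) = 0.01628, so power = Φ(2.850 − 1.96) = 81.3%. For R² = 0.10 the standard error is 0.01545, so power = Φ(3.004 − 1.96) = 85.2%.

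| Assumed R² | Power | Gain (points) |
|---|---|---|
| 0 | 81.3% | – |
| 0.05 | 83.2% | 1.9 |
| 0.10 | 85.2% | 3.9 |
| 0.15 | 87.1% | 5.8 |
| 0.20 | 89.0% | 7.7 |
| 0.25 | 90.8% | 9.5 |

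Starting from exactly 80%, the same formula gives 82.0%, 84.0%, 86.0%, 88.0% and 89.9% for R² of 0.05 to 0.25, which is a gain of up to 9.9 points.

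**Step 3: check by simulation.** Trials were simulated with one normally distributed prognostic score, 2000 per setting. The chi-square test was compared with the Wald test from the adjusted logistic regression. Monte Carlo error is about 1 point.

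| AUC of the score | R² | Gain at 1471 per arm | Gain at 1549 per arm |
|---|---|---|---|
| 0.61 | 0.03 | 1.3 | 1.9 |
| 0.66 | 0.07 | 2.0 | 2.4 |
| 0.69 | 0.10 | 4.4 | 2.6 |
| 0.73 | 0.13 | 4.8 | 5.3 |
| 0.76 | 0.18 | 6.9 | 7.4 |
| 0.79 | 0.23 | 7.8 | 7.7 |

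The simulation agrees with the formula within its error. All figures treat infants as independent. Infants of a multiple birth go to the same arm, so absolute power may be lower than shown.

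**The case against.** The strongest reply is that nothing here is wrong. A chi-square test on a randomised binary outcome is valid, controls type I error, matches the power calculation and reaches its target. That stands. A reader might infer that the trial is underpowered or the primary test faulty; Step 1 shows neither.

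Four further limits also stand:

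- **The size of the gain is not known.** A reader might take 4 to 8 points as established. That needs R² of about 0.10 to 0.20, which the documents do not give. Statistical analysis says about 17% of preterm infants die at home after discharge against medical advice, set against a 29% composite rate, and nothing shows how well gestational age or birth weight predicts those deaths.
- **Illness severity may not be a baseline value.** The list in Data collection mixes items from before and after randomisation and gives no scoring time.
- **Adjusted analyses are not absent.** Centre-adjusted models and the propensity-score regression are planned. They are conditional, and none is the primary analysis.
- **Chance imbalance is not bias.** It is random error already covered by the test's error rate, and its removal is part of the same variance reduction as R², not a second benefit.

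These points narrow the claim but do not remove the gain. Nor is spare precision idle: the Discussion allows for 10% drop-out. If those infants had no primary outcome (1549 × 0.90 = 1394 per arm), the formula in Step 2 gives 79.2% unadjusted and 83.2% at R² = 0.10.

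**Conclusion.** The point holds as a recommended improvement. The plan fixes an unadjusted primary test and uses gestational age and birth weight only as two-level interaction groups. A pre-specified adjusted primary analysis would raise power from about 81% to between about 83% and 91%, a gain of about 2 to 10 points.

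That range rests on three assumptions: an R² of 0.05 to 0.25, which is not in the documents; 1472 evaluable infants per arm; and independent infants. The direction of the gain is secure if the covariates are prognostic, but its size is not.

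**What to change.** In Statistical analysis, replace the primary test with a logistic regression of the composite on:

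- treatment;
- gestational age at birth and birth weight, both continuous, in a form stated in advance;
- NICU, as the stratification factor;
- the illness severity score, only if it is confirmed to be scored before randomisation.

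Use standard errors that allow for siblings allocated together, for example clustered by mother. Leave out anything that can change after randomisation, including receipt of probiotics unless it is fixed beforehand.

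A plain logistic model estimates a conditional odds ratio. Report the standardised risk difference and risk ratio from it instead, so that the result still answers the 16% relative reduction in the sample size. Keep the chi-square test as the unadjusted supporting analysis.

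The cost is modest: no extra infants, some analysis code, a pre-specified covariate form, and simple imputation for the few covariate values that may be missing. Recruitment has begun according to Trial status, so the change needs a protocol amendment, approved before any unblinded analysis.

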## Methods/Design

### Study design

Our study will be a prospective, multicenter, blinded, randomized, controlled trial (RCT) designed in accordance with the Standard Protocol Items: Recommendations for Interventional Trials (SPIRIT 2013; Additional file 1) [14] and the Consolidated Standards for Reporting of Trials CONSORT guidelines [16]. Mothers who consent to participate in the study will be randomly assigned to the intervention (fresh milk) group or the control group. In the fresh milk group, mothers will be asked to provide at least two feeds of fresh milk (i.e., within 4 h of milk expression) per day. In the control group, mothers will follow the usual protocol for the collection, freezing, and use of human milk, and the current NICU standards of human milk handling and feeding will apply.

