### Study population

The study population will include infants born at < 30 weeks’ gestation who never received infant formula, are admitted to one of the 29 participating tertiary NICUs in China, have parents who consent to the study, and have mothers who are willing to provide at least two feeds of fresh milk daily, 7 days a week until the infant is 32 weeks’ corrected age. Infants with major congenital anomalies or receiving palliative care, infants with mothers who are too ill to provide fresh human milk in the first week postpartum or are unable to provide at least two feeds of fresh milk a day, infants with congenital *Cytomegalic virus* (CMV) infection, and infants whose mothers have blood CMV-IgM (+) or CMV-DNA (+) or are unwilling to consent will be excluded. Congenital CMV-infection is defined as positive CMV NAT (or positive viral culture obtained from clinician-ordered testing) in blood or urine within 2 weeks of life [20].

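### The primary chi-square test and the sample size treat infants as independent, although mothers are randomised with siblings in one arm and randomisation is blocked within NICU

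*Protocol article*

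**What the plan says.** The Statistical analysis section names the primary test: for the difference "in the rate of the primary outcome between the control and fresh human milk groups, we will use the chi-square test". The Sample size section bases its power on the same test: 29% in the control arm, a 16% relative reduction, 1549 infants per arm, 80% power, 5% loss to follow-up. It mentions neither multiple births nor a design effect.

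The design is described differently:

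- Study design: "Mothers who consent to participate in the study will be randomly assigned to the intervention (fresh milk) group or the control group".
- Randomization and blinding: "Infants from multiple-birth pregnancies will be randomized to the same group".
- Same section: "A blocked randomization method stratified by NICU will be used to assign infants to either the control or fresh milk groups".
- Study population: infants "admitted to one of the 29 participating tertiary NICUs in China". Multiples are not excluded.

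NICU appears only under secondary analyses. Treatment effects are plotted by centre, and then: "If variation is observed, we will further compare the binary outcomes using the Cochran-Mantel-Haenszel test to account for the effect of center". Fixed-effect regressions without and with a treatment-by-centre interaction may follow, then generalized estimating equations (GEE) to allow for centre. The propensity-score regression for the primary outcome is optional and aimed at drop-out.

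**The concern.** An infant-level chi-square is exact to the design only if each infant is randomised separately and without strata. Neither holds here, and the two departures act in opposite directions.

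- **Siblings in one arm.** If their outcomes are positively correlated, the infants carry less information than their number suggests. The computed standard error is too small, the false-positive rate exceeds 5%, and the stated power is too high.
- **Blocking within NICU.** Blocking balances the arms within each unit, so variation between units does not contribute to the difference between arms. The plain test still counts that variation, so its standard error is too large and its size falls below 5%.

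The p value affected is the trial's one confirmatory p value. The choice of test is stated in the article, so this is not a detail left to a fuller plan.

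**Working it through.** **Step 1. Reproduce the stated sample size.** From Sample size: p1 = 0.29, p2 = 0.29 × 0.84 = 0.2436, difference 0.0464, mean 0.2668; two-sided 5%, 80% power.

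n = [1.96 √(2 × 0.2668 × 0.7332) + 0.8416 √(0.29 × 0.71 + 0.2436 × 0.7564)]² / 0.0464² = 1426 per arm.

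The continuity correction raises this to 1468, and 1468/0.95 = 1546, against 1549 stated. The same corrected formula for 17% against 12.75% gives exactly the 1146 per arm that Statistical analysis states for actively treated infants. The calculation is thus one for independent infants, with no visible allowance for siblings.

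**Step 2. Siblings alone.** The article gives neither the share of multiples nor a sibling ICC, so both are assumed. With s the share of infants who are twins:

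- design effect DE = 1 + s × ICC
- true size = 2 × [1 − Φ(1.96/√DE)]
- power after loss uses 0.95 × 1549 = 1471 infants per arm, divided by DE, without continuity correction. At DE = 1 this is 81.2%.

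An ICC towards 0.5 is not fanciful. Statistical analysis says about 17% of infants die at home after discharge against advice, plausibly a family decision. As an illustration, suppose those deaths fall within the outcome window, the overall rate is 29%, everything else is independent, and siblings' discharge decisions correlate at r. The other-event rate is (0.29 − 0.17)/0.83 = 0.145. The outcome ICC is then (1 − 0.145)² × 0.17 × 0.83 × r / (0.29 × 0.71), about 0.5r.

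**Step 3. NICU strata.** Ignoring strata multiplies the true variance, relative to the computed one, by about 1 − c, where c is the NICU ICC. A between-NICU SD of 0.5 on the logit scale gives c = 0.048 and, without multiples, a size of about 4.5%. An SD of 0.2 gives c of about 0.29 × 0.71 × 0.2² = 0.008.

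**Step 4. Both together.** The variance ratio is DE × (1 − c). For s = 0.30, ICC = 0.5 and SD 0.5 it is 1.15 × 0.952 = 1.095, and 2 × [1 − Φ(1.96/√1.095)] = 6.1%.

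| s | Sibling ICC | DE | Size, siblings only | Size, NICU SD 0.2 | Size, NICU SD 0.5 | Power after 5% loss (siblings only) |
|---|---|---|---|---|---|---|
| 0.20 | 0.1 | 1.02 | 5.2% | 5.1% | 4.7% | 80.5% |
| 0.20 | 0.3 | 1.06 | 5.7% | 5.6% | 5.1% | 78.9% |
| 0.30 | 0.3 | 1.09 | 6.0% | 5.9% | 5.4% | 77.8% |
| 0.30 | 0.5 | 1.15 | 6.8% | 6.6% | 6.1% | 75.6% |

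**Step 5. Simulation check.** With 29 NICUs, blocks of four, about 3098 infants and 12,000 replicates (Monte Carlo SE about 0.2 points), the plain chi-square had these sizes, in row order:

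- SD 0.2: 5.1%, 5.6%, 6.4% and 6.8%
- SD 0.5: 5.0%, 5.3%, 5.3% and 6.0%

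A separate run of 5000 replicates at s = 0.30, ICC 0.5 and SD 0.5 compared three tests: plain chi-square 5.9%, Cochran-Mantel-Haenszel by NICU 6.6%, and a NICU-stratified comparison with variance clustered on the mother 4.6% (Monte Carlo SE about 0.3 points). Allowing for NICU alone removes the conservative error and leaves the anti-conservative one.

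**The case against.** The strongest reply is that the two errors largely offset, so the plain test is close enough. Much of that stands. At 20% multiples and an ICC of 0.1-0.3 with SD 0.5, the size is within sampling error of 5% or only slightly above it. A clear excess needs more multiples with a higher sibling correlation, or NICUs that differ little. Offsetting is not guaranteed, however, because it rests on three quantities that the article does not give.

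Other objections limit what can be claimed:

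- A reader might infer that the trigger for the Cochran-Mantel-Haenszel test is backwards, since it is called when effects seem to vary. The article does not support that. The test is valid under the null without a common effect, and the plan goes on to examine the interaction. What stands is that allowing for NICU is secondary and data-dependent.
- A reader might infer that no listed method could cover siblings. If the GEE clusters on NICU with robust variance, siblings within a NICU are covered. But it is specified for centre, is conditional, and is not the primary test.
- A reader might count the absence of gestational age from the primary test as an error. An unadjusted comparison is valid; adjustment would only gain precision.
- Trial status says recruitment began on January 1, 2019, so a change means amending a running trial.

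**Conclusion.** The mismatch between design and primary test needs no assumption: it follows from Study design, Randomization and blinding, Sample size and Statistical analysis read together. Its consequence is modest and uncertain. Under the assumed ranges (20-30% multiples, all taken as twins; sibling ICC 0.1-0.5; between-NICU SD 0.2-0.5), the true size is about 5% to 7%. Power after 5% loss, from the sibling design effect alone, is about 80% down to 76%.

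A reader might conclude that the trial will run at 7% or that its false-positive rate is certainly inflated. The article does not support either. The upper figure needs the highest assumed share of multiples and ICC with little variation between NICUs, and at the low end the test is essentially correct. The sign of the net error cannot be settled from the article. The reason to act is that a test matching the design removes the question at almost no cost.

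**What to change.** 1. Make the primary analysis one unconditional comparison in all randomised infants, stratified by or adjusted for NICU (for example logistic regression or GEE), with variance clustered on the mother. Report the marginal risk difference with its 95% confidence interval.
2. Remove observed variation as the condition for allowing for NICU. Keep the interaction analysis as an examination of heterogeneity.
3. Keep the infant-level chi-square as a sensitivity analysis.
4. In Sample size, state the assumed share of multiples and sibling ICC, and restate the power with the resulting design effect. Do not raise the target: the article's own rate gives 2 × 1438 = 2876 infants in two years, already short of 3098.
5. Carry mother-level clustering through to the secondary comparisons, which are also made at infant level.

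Gestational age as a covariate is an optional precision gain.

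The cost is a protocol amendment, made before unblinding, and a slightly less favourable stated power. The data must hold a family identifier linking siblings; Data collection does not name one, though the mother's bar code on milk containers suggests that it is available.
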